##### Enhanced Wait-List Control (eWLC)

The participants placed on the wait-list may avail of several resources suggested to them. These include lecture series on stress control, list of self-help books and the possibility to have a 30-min consultation with a psychologist in an advice clinic. The uptake of those resources is self-directed. The record will be taken of what resources, if any, participants actually availed of.

### Eligibility criteria

Clients will be selected based on the following inclusion/exclusion criteria. Preliminary screening of the existing referrals will include potential participants that will be of minimum age of 18 years old, fluent in English, have access to the Internet and an email account and have symptoms of anxiety and/or depression referenced as primary presenting problem(s) on the referral form from the General Practitioner (GP). The full inclusion criteria will then include a score of ≥ 8 on OASIS [32, 38] and/or a score of ≥ 8 on ODSIS [33]. Exclusion criteria will include an increased risk of suicidality intent or ideation (at least moderate scores on the M.I.N.I [39]. and/or a score > 2 on item 9 from the PHQ-9 [40], psychotic disorder, manic or hypomanic episode, bipolar disorder, eating disorder, anti-social personality disorder and/or alcohol/substance use disorder as indicated by the M.I.N.I., references to cognitive impairment on the referral form, or a receipt of another psychological treatment at the start of the study. It is envisaged that pharmacological treatment during the treatment period will be allowed provided that it was stabilized 6 weeks prior the start of being involved in the study. Any changes to it will be monitored afterwards.

### Recruitment procedures

#### Participant recruitment

Recruitment has begun in November 2021 and will run until the required sample size is reached. This is estimated to take between 18 and 24 months. Potential participants will be selected in two ways: from the routine primary care service’s referral/waiting list. An initial telephone screening interview will be conducted by a clinician (psychologist, trainee psychologist or assistant psychologist) working on the research team to determine if the individual meets the preliminary eligibility criteria. If eligibility criteria are met, the individual will be invited to participate in the study. An overview of the study will be provided, and the individual will be given the opportunity to ask questions about the study. Those who wish to participate will be emailed a link to the study’s website, through which they will be asked to provide informed consent digitally. Participants will be told that they may withdraw from the study at any time. Once consent is obtained, a follow-up structured interview will be scheduled, where a clinician (psychologist, trainee psychologist or assistant psychologist) will administer the Mini-International Neuropsychiatric Interview (M.I.N.I.) as well as other standardized questionnaires. Clinicians administering the M.I.N.I. will undergo a specific training programme prior to using the tool to ensure the quality standard is maintained. The M.I.N.I. evaluation will allow the clinician to assign participants into diagnostic categories. Following the recruitment procedure, participants will be randomly allocated into the treatment or eWLC group using a ratio of 2:1. Participants will then be advised to which group they have been assigned (for the flow of participants, see the CONSORT Fig. 1). Participants will be instructed on next steps for their treatment group.

**Fig. 1 Fig1:**
[figure not shown]
CONSORT flow chart

#### Clinician recruitment

All participating clinicians/supporters (assistant psychologists and trainees psychologists who will be offering asynchronous support for clients utilizing iUP (Supporters) and psychologists who will be offering supervision of assistant/trainee psychologists) from the primary care site will be briefed on relevant aspects of study design and objectives. They will participate as both clinical professionals supporting treatment and will also be involved in the research itself.

### Risk management

The iUP programme is not intended to provide crisis support or intervention to individuals who are at risk of suicide. Risk will be assessed, monitored and managed as part of an ongoing duty of care to all participants in the study and this will correspond with the site’s own governance and risk procedures. The M.I.N.I. and PHQ-9 measure will be used to provide an initial risk assessment whereby individuals who score > 2 on the item relating to suicide and self-harm will be excluded from the study and referred to get additional support. The score on PHQ-9 will also be reviewed at weeks 4, 8, 12 and also at weeks 16, 20 and 24 and in case of elevated risk (score > 2 on the item relating to suicide and self-harm), further follow-up questions will be administered (Do you have any current plans to end your life? Have you made any current preparations toward ending your life? How likely is it that you will act on these thoughts or plans to end your life?) and this will be brought to the attention of clinical supervisor who will determine the next steps (e.g. follow-up with the client, referral). Scores on measures will be reviewed at the end of treatment to determine whether the participant can be discharged or will be referred for further treatment within the service. Any further referrals will be recorded.

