#### Intervention

##### Internet-based Unified Protocol (iUP)

The iUP is an eight-module online intervention that is based on the second edition of the UP [21, 36]. It includes the five core CBT modules in the UP that target neuroticism (i.e. negative affect and aversive reactivity to emotions) and subsequent emotion motivated avoidant coping [37]. See Table 1 for an overview of the modules. The programme is self-directed, so the client can proceed through the programme at their own pace. The recommended time to spend on a module is initially 1 week, but starting with module 3, and for the rest of the core modules in the UP (Table 1), the supporter (see below) may suggest extra time, 2 or more weeks. Supporters particularly recommend that participants spend 2–4 weeks on module 7 (Emotion Exposures). Specific recommendations from supporters will also consider participant pace, progress and engagement with the programme (e.g. if someone does not complete a specific module 1 week, they may be encouraged to complete it the following week). This intervention will be delivered on the SilverCloud platform. SilverCloud Health is a global leader in the development of computerized psychological interventions for depression, anxiety, stress and comorbid long-term conditions. The intervention will be delivered on a Web 2.0 platform using media-rich interactive content. Consistent with other SilverCloud programmes, each module follows a structured format and includes videos, a psychoeducational content, interactive activities and tools, instructions for practicing skills and summaries of the modules. Clients’ progress and use of the iUP will be reviewed by a supporter, who will provide feedback on the client’s use of the programme. Their support will consist of email messages to the clients that provide encouragement and suggestions for the use of the programme. The feedback will be provided every 6 to 10 days. The supporters will be assistant psychologists and/or trainee psychologists. They will be under supervision of a qualified psychologist. All participating clinicians will be trained by an UP trainer in the delivery of support for iUP and in addition will receive training on the platform and how to deliver supporter reviews to participants.

**Table 1 Tab1:** Modules in the Internet-based UP

Module name	Brief description

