### Governance and oversight of the trial

The Trial Management Group (TMG) will be established to oversee day-to-day operations of running the trial such as training of supporters, recruitment of participants, clinical governance and ethical issues, adverse events and data management processes. The TMG will meet quarterly or as needed. It will consist of the principal investigator (PI), co-principal investigator, trial managers and service representatives. The TGM will regularly discuss any potential changes to the trial protocol that will then be brought to the Trial Steering Committee (TSC). The TSC will consist of the abovementioned members of the TMG, an independent academic, a public health service manager responsible for the services in the area and a service user representative. The TSC will meet every 6 months over the course of the project and will have the function of overseeing the project. The PI will report to the committee on progress regarding the trial and seek perspectives from the TSC regarding any issues arising.

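### After entry, the questions on suicide plans, preparations and likelihood of acting, and the supervisor alert, are required only at a suicide-item score above 2, so new risk at a score of 2 or less meets no stated trigger, although entry also excludes at least moderate M.I.N.I. suicidality whatever the item score

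*Protocol article*

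**What the plan says.** At entry, the Eligibility criteria section excludes people with "an increased risk of suicidality intent or ideation (at least moderate scores on the M.I.N.I [39]. and/or a score > 2 on item 9" of the PHQ-9. Either condition alone is enough.

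After entry, the Risk management section has the PHQ-9 reviewed at weeks 4, 8, 12, 16, 20 and 24. It then states: "in case of elevated risk (score > 2 on the item relating to suicide and self-harm), further follow-up questions will be administered". There are three questions: current plans, current preparations, and "How likely is it that you will act on these thoughts or plans to end your life". The result goes to the clinical supervisor, who decides the next steps. Table 2 marks the M.I.N.I. at enrolment only.

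The article also states general safeguards:

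- A duty of care tied to the site's governance and risk procedures: "Risk will be assessed, monitored and managed as part of an ongoing duty of care to all participants in the study".
- A closing review: "Scores on measures will be reviewed at the end of treatment to determine whether the participant can be discharged or will be referred" onward within the service.
- A Trial Management Group whose remit includes "clinical governance and ethical issues, adverse events and data management processes".
- For iUP clients, supporters who give feedback every 6 to 10 days: "They will be under supervision of a qualified psychologist".
- For the waiting list, "the possibility to have a 30-min consultation with a psychologist in an advice clinic", taken up at the participant's own initiative.

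**The concern.** The entry rule accepts that a person can have disqualifying suicide risk while scoring 2 or less on the questionnaire item; that is what the M.I.N.I. limb of the exclusion is for. After entry that limb is gone, and the item score alone decides whether anyone must ask about plans and preparations.

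The Risk management section says the iUP is not meant as crisis support for people at risk of suicide. The three questions are the stated means of learning whether a participant has moved into that group. At an item score of 2 or less the interim reviews require no step that would bring out a plan or a preparation. What is at stake is participant safety in both arms. Sample size, power and the treatment estimates are unaffected.

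**Working it through.** The plan gives no figure to reproduce, so the check is a comparison of rules, followed by a count of the workload.

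**Rules side by side**

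- Entry (Eligibility criteria): exclude if M.I.N.I. suicidality is at least moderate OR item 9 > 2.
- After entry (Risk management): ask the three questions and alert the supervisor if item 9 > 2.

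| State of the participant | At entry | If it arises after entry |
|---|---|---|
| Item above 2, any M.I.N.I. level | Excluded | Questions and alert required |
| Item 2 or less, suicidality that the M.I.N.I. would rate at least moderate | Excluded | No stated trigger |
| Item 2 or less, suicidality below moderate | Not excluded on this ground | No stated trigger |

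The middle row is the gap. The Risk management section's own summary of the entry rule gives a cut-off only for the item score; the Eligibility criteria section is the formal text and is used here.

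**Do the general safeguards fill the middle row?**

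- The duty of care carries no threshold or action in this document, and the site procedures are not shown.
- The closing score review comes after the interim visits and is described as deciding discharge or referral.
- Supporter contact is by email and concerns use of the programme. No risk enquiry is stated.
- The advice clinic is optional.
- Apart from the telephone interview before therapy, screening and assessment information is gathered online (Data management). No live assessment is scheduled after entry.

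Each of these may catch some cases. None states an interim action at a low item score.

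**Readings governed by the rule**

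- Inputs: 120 participants, 80 of them iUP (Design); three reviews in both arms and three more for iUP (Table 2).
- Scheduled readings: 120 × 3 + 80 × 3 = 360 + 240 = 600.
- With 30% missing at every visit: 600 × 0.70 = 420. This is an assumption; the Sample size section gives 30% at the primary endpoint only.

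**Extra question sets under the fix**

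The share of readings that are non-zero but not above 2 is not in the document. The assumed range is 10% to 30%.

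| Assumed share | Of 600 | Of 420 |
|---|---|---|
| 10% | 60 | 42 |
| 20% | 120 | 84 |
| 30% | 180 | 126 |

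**Rate per month**

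- Recruitment from 24.11.2021 to 31.12.2023 (Trials status): 767 days.
- Add 24 weeks of follow-up for the last entrant: 767 + 168 = 935 days.
- Subtract the 28 days before the first week-4 review: 935 − 28 = 907 days, or about 29.8 months.
- Lowest: 42 / 29.8 = 1.4 a month. Highest: 180 / 29.8 = 6.0 a month.

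Scores above 2 are already alerted, so each extra set can add at most one notification. Extra notifications therefore cannot exceed the same 1.4 to 6.0 a month.

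**The case against.** The strongest reply is that this is a condensed article that points to site risk procedures, and triage rules for lower scores may be written there. That stands as a limit: the check shows that no trigger below the cut-off is printed here, not that none exists. It does not remove the point. The article has not left the rule to another document; it fixes the instrument, the visits, the cut-off, the questions and the route to the supervisor, and the concern is with the cut-off it fixed.

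A second reply is that screening people out of a programme not meant for crises differs from deciding when to escalate someone already in care, and that the item cut-off is the same before and after entry. This also stands in part. A reader might infer that the two sections contradict each other, or that the M.I.N.I. ought to be repeated. The documents support neither: the rules serve different purposes, and giving the M.I.N.I. once is a reasonable choice.

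Third, the article does not print the response range or wording of item 9, so how serious a score of 2 or less is cannot be judged from the text. That is correct, and the point does not rest on it. It rests on the entry rule, which treats some risk at those scores as disqualifying.

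Two further inferences go too far. One is that any suicide risk on the M.I.N.I. excludes; the text says at least moderate. The other is that the questions are barred at lower scores; they are only not required there, and the PHQ-9 is reviewed at every listed week whatever its value.

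**Conclusion.** The point holds as a gap in safety monitoring. A risk state that would keep someone out of the trial meets no stated trigger if it develops later with an item score of 2 or less, in either arm. General duty of care and site procedures may catch some of these cases.

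Its clinical size is unknown. The article gives nothing from which to estimate how often new risk arises at low item scores. A reader might take the 600 scheduled readings (or 420 with 30% missing throughout) as a measure of missed risk. They count forms that the rule governs, and the 1 to 6 sets a month is the workload of the remedy under an assumed 10% to 30% share. Neither counts missed cases.

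The case for change is that the remedy is cheap and uses questions already written. Confidence is medium, because the site procedures are not shown.

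**What to change.** In the Risk management section, at weeks 4, 8 and 12 in both arms and at weeks 16, 20 and 24 for iUP:

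1. Ask the three existing questions at any non-zero score on the suicide item.
2. Alert the clinical supervisor for any of: an item score above 2 (as now); any current plan; any current preparation; any answer to the likelihood question other than the lowest option (no, or not at all likely). The article does not print answer options for that question, so the lowest option should be written down.
3. State that risk at an item score of 0 still relies on the general safeguards. The change narrows the gap and does not close it there.

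The cost is a wording change and a new prompt rule, with no new instrument, visit or staff role. The downside is about 1 to 6 more question sets a month under the stated assumptions, and at most that many more notifications.

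The change follows the existing visit schedule. It adds nothing for waiting-list participants who take up iUP after week 12, since Table 2 schedules the later assessments for the iUP arm only.

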### Randomization

Following the initial assessment and providing that the participant meets criteria for being included in the study, participants will be randomly allocated at an individual level using an algorithm developed by a computer scientist [41] and executed independently of the research team, employing random permuted blocks using block sizes of 6, and including stratification within a 2:1 allocation ratio between treatment and waiting list control groups. Post assessment, the clinician/researcher administering the M.I.N.I. opens concealed allocation and will then inform the participant of their allocation into either the wait-list or treatment group. The clinicians/supporters carried out the support of the clients in the intervention could not be blinded to allocation for practical reasons; however, the clinicians/researchers conducting the pre-trial assessment are going to be blind to the condition allocation during the assessment.

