## Method

### Design

The current study will employ a parallel-group, exploratory randomized controlled trial design. The study will follow the CONSORT statement [29], CONSORT E-Health guidelines [30] and the SPIRIT guidelines (Standard Protocol Items: Recommendations for Interventional Trials) [31]. Participants will be randomly assigned to (a) the internet-based Unified Protocol (iUP), or (b) enhanced waiting list control (eWLC). Randomization will follow a 2:1 allocation ratio, with sample size calculations suggesting a required sample of 120 (iUP=80; eWLC=40). Assessments will take place at baseline, 4 weeks, 8 weeks and 12 weeks from baseline. For ethical reasons, the eWLC group participants will be offered iUP treatment after 12 weeks. iUP group participants will be followed up at 16 weeks, 20 weeks and 24 weeks from baseline, so that we can examine (short-term) stability of any effects achieved.

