### Participants and study setting

Participants will be adults (18 years old or older) with anxiety and/or depressive symptoms that attend primary care services in Ireland to seek mental health care. To be eligible, participants will have to have a score of ≥ 8 on the Overall Anxiety and Severity Impairment Scale (OASIS) [32] and/or a score of ≥8 on the Overall Depression Severity and Impairment Scale (ODSIS) [33]. The study will take place in a naturalistic setting within a Dublin-based primary care psychology service which is part of the Health Service Executive (HSE) in Ireland. Referrals are made via General Practitioners (GP), allied services, or self-referral. Average wait-list times can range from 3 to 12 months. At the end of the wait-list period, the service usually offers an initial intake assessment followed by an individual care plan, including individual and/or group psychotherapy, delivered by psychologists trained in a variety of therapeutic modalities. The service offers some support for clients on the wait-list (including a lecture series on stress control, a list of self-help books and the possibility to have a 30-min consultation with a psychologist in an advice clinic).

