### Sample size

Sample size was determined in relation to the planned analysis of primary outcomes (i.e. linear mixed models of anxiety/depression severity) and calculated in the R package ‘powerlmm’ [34]. Model parameters (random intercept/slope, residual variance) required for this calculation were estimated from similar data from a previous trial on a transdiagnostic intervention in primary care [26]. Given a 2:1 randomization ratio, longitudinal data collected at four timepoints across both groups, 30% research attrition at the primary endpoint and a moderate post-treatment between-group effect size of *d*=0.5 in line with previous research [21, 35], a sample size of 120 (iUP=80, WLC=40) was estimated to yield sufficient statistical power of 0.83 (a Bonferroni-adjusted *p* value of 0.025 to account for two primary outcome measure would reduce power to 0.75; at a lower attrition rate of 20% rather than 30%, power of 0.80 would be reached even with the Bonferroni-adjusted *p* value).

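### One published block size of 6, with allocations opened by the eligibility assessor, lets a fully informed observer know up to 28.9% of allocations in advance

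*Protocol article*

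**What the plan says.** All references are to the protocol article.

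- **Block size and ratio.** Randomization specifies individual allocation, "employing random permuted blocks using block sizes of 6", and "including stratification within a 2:1 allocation ratio between treatment and waiting list control groups". Only the size 6 is given. The stratification factors and the number of strata are not named.
- **Sample.** Design states: "Randomization will follow a 2:1 allocation ratio, with sample size calculations suggesting a required sample of 120 (iUP=80; eWLC=40". Sample size uses the same 80:40 split.
- **Setting.** Participants and study setting names "a Dublin-based primary care psychology service which is part of the Health Service Executive (HSE) in Ireland", that is, one service.
- **Who opens the allocation.** After the assessment, "the clinician/researcher administering the M.I.N.I. opens concealed allocation and will then inform the participant of their allocation".
- **What that person decides.** Eligibility criteria takes several exclusions from the same interview, among them "anti-social personality disorder and/or alcohol/substance use disorder as indicated by the M.I.N.I".
- **Safeguards.** Randomization says that the algorithm is run outside the research team, that the allocation is concealed, and that pre-trial assessors are blind to condition while they assess. Supporters are not blinded.
- **Roles.** Of the participating clinicians and supporters, Clinician recruitment says: "They will participate as both clinical professionals supporting treatment and will also be involved in the research itself".

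**The concern.** Concealment hides the code for the current participant. It does not hide what earlier codes imply. When every block has the same known size and composition, the rest of a block is determined once two eWLC or four iUP allocations have appeared in it. Under the stated procedure an assessor learns every allocation that he or she opens, because blinding applies only during the assessment of the current person.

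The same assessor applies the interview-based exclusions. One who could foresee the next arm could bring forward, postpone or exclude a borderline person accordingly. The groups might then differ at entry in ways that were not recorded, and the analysis model could not fully correct for that. At stake is the comparability that randomization is meant to provide.

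**Working it through.** The protocol gives no predictability figure, so there is none to reproduce. The split does agree with the block: 120/6 = 20 blocks, 20 × 4 = 80 iUP and 20 × 2 = 40 eWLC.

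**Inputs.** Block size 6 and ratio 2:1 (Randomization); N = 120 (Design, Sample size). Assumptions for the ceiling: one stratum, and an observer who knows the block size and every earlier allocation.

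**Certain places.** A block of four iUP and two eWLC has C(6,2) = 15 equally likely orders. A place is certain in advance when all remaining places belong to one arm, so the number of certain places in a block is the length of its final run.

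| Place in block | Chance that it is certain | Accuracy of the best guess |
|---|---|---|
| 1 | 0 | 66.7% |
| 2 | 0 | 66.7% |
| 3 | 1/15 = 6.7% | 66.7% |
| 4 | 3/15 = 20% | 73.3% |
| 5 | 7/15 = 46.7% | 73.3% |
| 6 | 15/15 = 100% | 100% |

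- Certain places per block: (1 + 3 + 7 + 15)/15 = 26/15 = 1.733. As a share: 1.733/6 = 26/90 = 28.9%.
- Check by closed form: iUP 4/(2+1) = 1.333 and eWLC 2/(4+1) = 0.400, which sum to 1.733.
- Over 20 blocks: 20 × 1.733 = 34.7 of 120, made up of 26.7 iUP and 8.0 eWLC.
- Mean best-guess accuracy: (3 × 66.7 + 2 × 73.3 + 100)/6 = 74.4%. Always guessing iUP gives 66.7%.

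**Strata (assumed number, equal probability, N = 120, simulated).** Incomplete last blocks lower the certain share even with full tracking: 28.0% with 2 strata, 27.1% with 4, 25.3% with 8 and 23.4% with 12.

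**Partial sight (assumed number of assessors, simulated).** Here each assessor knows the block size and where blocks begin, but sees only the allocations that he or she opens. The certain share is 28.9% with one assessor, 5.9% with two, 2.5% with three and 1.4% with four.

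**Varying sizes (simulated lists of 120, one stratum).** Here the observer knows the possible sizes and all past allocations, but not the current size.

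| Block sizes | Certain in advance | Best-guess accuracy |
|---|---|---|
| 6 only | about 29% | about 74% |
| 3, 6, 9 | about 4% | about 74% |
| 6, 9, 12 | about 2–3% | about 72% |

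**The case against.** The arithmetic is not in dispute. The objections concern what it can bear.

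- **A reader might infer that about 29% of allocations are in fact known to staff.** The documents do not support that. The figure requires complete tracking within the stratum. With two assessors who see only their own allocations it is about 6%. No sharing of allocations within the team is described. This objection stands, and it makes 28.9% a ceiling.
- **A reader might infer that assessors and supporters are one small team.** The text labels the two roles separately, and nowhere gives the size of the team. The job grades overlap and supporters take part in the research, so overlap is possible, but it is not stated. The point does not need it, because the assessor opens the allocation in any case.
- **Certainty overstates the advantage.** Most forced places are iUP, already the likelier arm, and full knowledge raises best-guess accuracy only from 66.7% to 74.4%. This stands. Even so, the last place in a fully tracked block is always known, and about 8 eWLC allocations would be certain.
- **Unblinded self-reported outcomes might seem to aggravate this.** They do not bear on it. They raise measurement bias, whereas blinded outcomes would not undo selection at entry either.
- **Discretion is limited and allocation already comes last.** Entry rests on questionnaire cut-offs and a structured interview, consent precedes the M.I.N.I., and allocation follows assessment. The mixed model, which includes time and allows individual intercepts, partly addresses differences in baseline severity. These points narrow the opportunity without closing it: timing and borderline interview judgements remain, and the model cannot adjust for what was not measured. They do mean that no further rule on the order of assessment and allocation is needed.

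**Conclusion.** The point holds as a real but modest weakness in a stated design rule. A single published block size, in one service, with each allocation opened by the person whose interview decides several exclusions, leaves up to 28.9% of allocations knowable in advance to someone who knows the size and has followed every allocation in the stratum. The likely share depends on two things that the article does not give: the number of strata, and how many allocations each assessor sees. The first moves it to roughly 23–28% under 2–12 strata; the second can move it to a few percent. Independent execution and concealment of the current code are sound, but they do not address inference from past codes. Nothing in the document shows that selection took place. This is a cheap improvement to make, not an error that invalidates the trial.

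**What to change.** For any allocations still outstanding, the independent party who runs the algorithm should generate the unused part of the list with block sizes that vary at random in multiples of 3, so that 2:1 is kept (for example 6, 9 and 12). The sizes should not be disclosed to recruiting staff or published before recruitment closes.

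The main gain is in certainty: the share of allocations known in advance falls from about 29% to about 2–3% for a fully informed observer. Overall guessability changes little, from about 74% to 72%. Sizes of 3, 6 and 9 would leave best-guess accuracy at about 74%, so the larger set is preferable.

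The cost is regenerating the remaining list and accepting a slightly larger possible imbalance at the end of the trial or within strata. How many allocations this can reach is unknown: the trial status section gives 31.12.2023 as the approximate end of recruitment. If none remain, the trial report should state the fixed block size and who opened the allocations, and could compare baseline severity between predictable and unpredictable places in the list.
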